Oral multimorbidity will include the presence of moderated to severe periodontal disease, toothache and use of denture. Self-reported painful gums and loose teeth will be used as surrogates for moderate to severe periodontal disease. In cases of multiple responses, the most severe indicator will be used as the primary surrogate for periodontal disease. Participants who did not report the above oral health indicators will be considered periodontally healthy.

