Oral multimorbidity will include the presence of moderate and severe periodontal disease, tooth loss (as a continuous and categorical variable: being edentate versus dentate), number of decayed teeth (as a continuous and categorical variable: having no decayed teeth versus having one or more decayed teeth), self-reported oral pain in the past year (“very often”, “fairly often” or “occasionally” versus “hardly ever” or “never”) and self-report global oral health (“excellent”, “very good” or “good” versus “fair” or “poor”). Periodontal disease (moderate and severe versus mild or no periodontal disease) will be measured by the clinical attachment loss (CAL) and periodontal probing depth (PPD). Severe periodontitis is defined as having 2 or more interproximal sites with CAL 6 mm or greater (not on the same tooth) and 1 or more interproximal sites with PPD 5 mm or greater. Moderate periodontitis is defined as 2 or more interproximal sites with CAL 4 mm or greater (not on the same tooth) or 2 or more interproximal sites with PPD 5 mm or greater (also not on the same tooth). Mild periodontitis is defined as 2 or more interproximal sites with CAL 3 mm or greater and 2 or more interproximal sites with PPD 4 mm or greater (not on the same tooth) or 1 or more sites with 5 mm or more.

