#### Statistical analysis

Descriptive statistics will be used to summarise participants characteristics. For NHANES and RELACHS data, survey analysis procedures will be used to account for the sample weights, stratification and clustering of the complex sampling design to ensure representative estimates.

To answer the research questions on the presence of syndemic relationships, a structural equation modelling (SEM) technique will be utilised to conceptualise syndemic constructs and model complex relationships between directly observed and indirectly observed (latent) variables. The SEM technique has gained increasing popularity in syndemic research (30, 31). To use this technique, the following steps will be undertaken:

In step one, exploratory and confirmatory factor analyses will be used to identify the clustering nature and reduce the number of indicators (observed variables) under each theoretical construct. In step two, a SEM to predict premature mortality and all-cause hospitalisation, controlling for age, sex and ethnicity, will be run. Analysis will include identifying whether the indicators chosen to measure the latent constructs are acceptable. confirmatory factor analysis will be used to provide information on how indicator items measure underlying (latent) constructs. In step three of the analysis, SEM will be used to examine the direct and indirect relationships between the constructs. The goodness of fit (GoF) of the SEM model to the data will be assessed considering the indices of Comparative Fit Index (CFI) and Tucker-Lewis Index (TLI; where values >.90 indicate a good fit), root mean square error of approximation (RMSEA), and Standardised Root Mean Square Residual (SRMR; where value <.05 indicate a good fit). In step four, the synergistic (multiplicative) interactions between different latent constructs and measured variables will be tested using two-step estimation procedures (32).

To answer the question on whether syndemic relationships vary by age, sex and ethnicity, stratified analyses by age, sex and ethnicity will be performed.

Full Information Maximum Likelihood technique will be used as a pragmatic approach for data missing estimation for SEMs. This approach produces unbiased parameter estimates and standards errors (33). For UK BioBank and RELACHS datasets, stability of exposure data over time will be checked by calculating the intraclass correlation coefficients between baseline and follow up data.

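### The UK Biobank rule for scoring participants as periodontally healthy does not separate symptom-free, non-responding and toothless people, and needs reconciling with FIML

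*Protocol article*

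**What the plan says.** In the protocol article, UK BioBank methods, Syndemic constructs, the oral construct has three indicators: "Oral multimorbidity will include the presence of moderated to severe periodontal disease, toothache and use of denture". The periodontal indicator is not clinical: "Self-reported painful gums and loose teeth will be used as surrogates for moderate to severe periodontal disease". Everyone else is then assigned by default: "Participants who did not report the above oral health indicators will be considered periodontally healthy".

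The Statistical analysis section says of missing data: "Full Information Maximum Likelihood technique will be used as a pragmatic approach for data missing estimation for SEMs". It adds that this approach gives unbiased estimates and standard errors. It also makes the correlations between indicators matter, because the modelling begins with a selection of indicators: "exploratory and confirmatory factor analyses will be used to identify the clustering nature and reduce the number of indicators (observed variables) under each theoretical construct".

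The NHANES section places edentate status, decayed teeth (in categorical form, "having no decayed teeth versus having one or more decayed teeth") and clinically measured periodontitis in one oral construct. It does not say how edentate participants are coded on the last two.

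**The concern.** The default rule puts three different groups in one category:

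- people who answered and reported neither painful gums nor loose teeth, for whom healthy is a reasonable score;
- people who gave no answer, whose status is unknown;
- people with no teeth, who cannot report loose teeth and enter the healthy group unless they report painful gums.

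For the second group, a missing value is replaced by an observed zero before the model is fitted. FIML acts only on values left missing, so the properties the plan claims for it do not reach these participants.

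For the third group, the periodontal indicator is scored favourably while denture use is scored adversely. Part of the correlation between two of the three oral indicators then comes from the scoring rule. These correlations decide which indicators are kept and how they load. The oral construct is the new element of the proposed syndemic, and step four tests interactions between the latent constructs.

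**Working it through.** The documents give no prevalence, response rate or correlation for this point, so there is no stated figure to reproduce. Only the UK Biobank sample size (502,412) comes from the document. All other values are assumptions, varied to show the range.

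**1. Toothless denture wearers**

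Let b be the periodontal rate in people without dentures, a the rate in denture users who have teeth, s the share of denture users who are toothless, and d the prevalence of denture use. If toothless people all score 0, the coded rate in denture users is p1 = (1 − s)a. The overall rate is p = d·p1 + (1 − d)b, and

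phi = (p1 − b)·√[d(1 − d)] / √[p(1 − p)].

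Take b = 5%, a = 10% and d = 17%. Without toothless zeros (s = 0), p = 0.17 × 0.10 + 0.83 × 0.05 = 0.0585, and phi = 0.05 × 0.3756 / 0.2347 = 0.080. Under the rule:

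| Toothless share s | coded rate p1 | phi |
|---|---|---|
| 0 | 10% | +0.080 |
| 10% | 9% | +0.065 |
| 25% | 7.5% | +0.041 |
| 50% | 5% | 0.000 |
| 75% | 2.5% | −0.045 |

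The sign turns negative only if (1 − s)a < b, that is, s > 1 − b/a. For risk ratios a/b of 1.25, 1.5, 2 and 3, the thresholds are 20%, 33%, 50% and 67%. They do not depend on d: with a risk ratio of 2 and s = 50%, phi is 0.000 at d = 5%, 17% and 30%.

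**2. Painful gums in toothless people**

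Painful gums do not require teeth. If toothless people report them at rate g, then p1 = (1 − s)a + s·g. With g = 3%, phi is +0.025 at s = 50% and −0.004 at s = 75%. With g = 5%, equal to b, it is still +0.021 at s = 75% and does not reverse.

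**3. Non-response scored as healthy**

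Let m be the share not answering, unrelated to disease or denture use. The coded prevalence is (1 − m)p, so a true 5% becomes 4.95%, 4.75% or 4.0% at m = 1%, 5% or 20%. Each percentage point of non-response is 0.01 × 502,412 ≈ 5,024 people coded healthy without an answer.

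Starting from phi = 0.08, with p = 5% and d = 17%:

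| m | only the periodontal indicator set to 0 | all oral indicators set to 0 |
|---|---|---|
| 5% | 0.078 | 0.085 |
| 20% | 0.071 | 0.098 |
| 50% | 0.056 | 0.124 |

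The first column follows the text, which sets only periodontal status. The second goes further than the text and shows what happens if the same default is applied to the other items. Scoring non-response as absence then inflates the association instead of weakening it. The sign does not change in either column.

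**The case against.** **Not selected, rather than not answered.** The sentence before the rule deals with multiple responses, which suggests a tick-all-that-apply item. Not reporting may therefore mean that the person answered and did not select a symptom. On that reading there is no conflict with FIML. This is a fair reading, but the sentence does not say so, and it leaves the toothless group unresolved.

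**Which indicators are meant.** If the indicators referred to include denture use and toothache, a toothless denture wearer has reported one and falls outside the rule. The periodontal score is then undefined for that person unless painful gums or loose teeth are reported. This too needs a clarifying sentence.

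**Stronger readings.** A reader might infer that toothless people are scored as orally healthy. They are not: the rule covers periodontal status only, and denture use stays adverse. A reader might also infer a general sign reversal. In UK Biobank this needs a toothless share that the documents do not give, and non-response alone does not produce it.

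For NHANES, a reader might conclude that tooth loss must correlate negatively with decay and periodontitis. That follows only if edentate people are coded 0 on both, and the protocol states no such coding. Simulating that recode (one factor, loadings 0.6, 40% periodontal, 5% edentate) moves the edentate–periodontal correlation from +0.14 to −0.17. But the same recode gives about −0.18 when edentate status is unrelated to disease, so the assumed coding produces the result.

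**Consequences downstream.** No factor model or interaction was fitted. A split oral factor, an improper solution, or interactions biased towards zero are therefore not shown. The plan's own check that the indicators are acceptable might also catch a poorly behaving item, although it would not show that the scoring rule was the cause.

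**Conclusion.** The concern holds for the UK Biobank rule. This is an explicit scoring instruction, not a detail left for later. Read literally, it hard-codes non-response as healthy ahead of FIML. Even on the milder reading of not reporting, toothless denture wearers without painful gums are misclassified if the rule refers to the two periodontal symptoms.

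The expected effect is attenuation of the periodontal–denture association. Under the assumed 5% and 10% rates it is roughly halved when a quarter of denture users are toothless. Reversal is possible only at a large toothless share, above 50% at a risk ratio of 2, and is less likely if toothless people report painful gums. Non-response adds a smaller distortion at modest rates. The NHANES point is secondary: the handling of edentate participants should be aligned with whatever is decided for UK Biobank.

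**What to change.** **UK Biobank.** Score periodontally healthy only for participants who answered the question and endorsed neither painful gums nor loose teeth. Set non-response to missing so that FIML handles it. State which indicators the rule refers to. Because full-denture wearers may not be identifiable, add a sensitivity analysis that excludes denture users from the periodontal indicator. In that analysis no denture user has a periodontal value, so the data carry no information on the periodontal–denture correlation. Denture use should then enter as a separate observed variable and not as an indicator of the same factor.

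**NHANES.** Define decay and periodontitis in dentate participants only, and carry edentate status as a separate category. Do not code edentate people 0 on these indicators, and do not let FIML treat values that cannot exist as ordinary missing data.

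**Cost.** Recoding, a sentence or two per dataset, one sensitivity analysis and a slightly more complex oral measurement model. No new data are needed.

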#### Mediators

Mediators are health behaviours and lifestyle, and C reactive protein (as an indicator of systemic inflammation).

Health behaviours and lifestyle variables will include obesity (BMI>=30), alcohol intake (healthy versus unhealthy level; the former is defined as daily consumption of two drinks or fewer for men and women, according to the dietary guidelines in the UK - one drink contains 8g in the UK), smoking (healthy versus unhealthy levels; the former is defined as never smoked or smoking fewer than 100 cigarettes in life), physical activity (healthy versus unhealthy; the former is defined as 150 minutes of moderate-intensity physical activity weekly or 75 minutes of high-intensity physical activity weekly), poor appetite or overeating (Yes versus No), diet quality (healthy versus unhealthy level; the former is defined as meeting at least five out of the following ten dietary recommendations: 3 servings/day of fruit, 3 servings/day of vegetables, 3 servings/day of whole grains, ≥2 servings/week of (shell)fish, 2 servings/day of dairy, 2 servings/day of vegetable oils, ≤2 servings/day of refined grains, ≤1 serving/week of processed meats, ≤2 servings/week of unprocessed meats, and no sugar-sweetened beverages) (26, 27), trouble falling/staying asleep or sleeping too much (Yes versus No), ever addicted to any substance or behaviour (Yes versus No), and lifetime number of sexual partners.

The level of C-reactive protein (CRP) is used as a marker of bodily (systemic) inflammation and presented in mg/L.

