Social adversity precipitates and exacerbates clusters of mental and physical diseases and conditions (**Figure 1**). For example, socioeconomic adversity (such as having low income, being unemployed or living in a deprived area) and traumatic events (such as adverse childhood experiences, being a victim of physically violent crime or sexual assault) are linked to compounded mental and physical conditions via systemic inflammation and behavioural pathways (10, 11). The situation can be further compounded by barriers to accessing healthcare (12). For instance, people with severe mental illness may experience under-recognition and under-treatment of physical conditions such as cardiovascular disease (12–14). In turn, these clustering mental and physical conditions reinforce each other through bidirectional interactions, that are also shaped by the social and contextual factors, leading to multiplicated mortality and morbidity burdens (8).

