#### Design and study population

UK Biobank database comprises prospective biomedical data from 502,412 participants living across the UK and aged between 40 and 69 years at the time of recruitment (2006 to 2010). It benefits from data linkages to other health related records: primary care data, hospital admission data and cancer and death registries.

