#### Syndemic constructs

Syndemic constructs include social adversity (socioeconomic adversity and traumatic events) and mental, physical and oral multimorbidity.

Socioeconomic adversity will be measured by socioeconomic position (SEP) indicators at individual, household and neighbourhood (area) levels: education, employment, income and deprivation. Education is measured at an individual level and will be categorised into high (college/vocational training or above) and low (A levels, AS levels, or equivalent; O levels, GCSEs, or equivalent; CSEs or equivalent; NVQ, HND, HNC, or equivalent; other professional qualifications; and “none of the above”). Employment status is measured at an individual level and will be grouped into: employed (including those in paid employment or self-employed, or doing unpaid or voluntary work) and unemployed (including being retired, full or part time students, unemployed, looking after home and/or family, or unable to work because of sickness or disability). Income is measured by the annual total household income before taxes are deducted. It will be categorised into 0 (>£100,000), 1 (£52,000-£100,000), 3 (£31,000-£51,999), 4 (£18,000-£30,999), and 5 (<£18,000). Area deprivation is measured by Townsend deprivation index quintiles. The two quintiles with the highest area deprivation scores will be scored 1 (indicating high levels of area deprivation), and the rest of quintiles will be scored 0 (indicating low levels of area deprivation).

Traumatic events will include felt hated by family member as a child, did not feel loved as a child, physically abused by family as a child, sexually molested as a child, no one to take to doctor when needed as a child, victim of physically violent crime, victim of sexual assault, witnessed sudden violent death, belittlement by partner or ex-partner as an adult, physical violence by partner or ex-partner as an adult, sexual interference by partner or ex-partner without consent as an adult, and been involved in combat or exposed to war-zone.

Mental multimorbidity will include mood disorders and severe mental illness (ICD-10 codes: F20-F29; F31; F33-34).

Physical multimorbidity will be measured using Ronaldson et al. approach that comprises a total of 36 long term physical health conditions (**Supplementary Table 1**) (22).

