#### Syndemic constructs

Syndemic constructs include social adversity (socioeconomic adversity) and mental, physical and oral multimorbidity. No data is available in NHANES on traumatic events.

Socioeconomic adversity will be measured by SEP indicators at individual and household levels: education, employment, occupation, income and health insurance. Education is measured at an individual level and will be categorised into high (college or above) and low (high school diploma or below). Employment status is measured at an individual level and will be grouped into: employed (working at a job or business or with a job or business but not at work) and unemployed (looking for work or not working at a job or business). Occupation is measured using socioeconomic index, which is based on the employees’ earnings, education level and prestige. It will be categorised based on the median into upper and lower level and unemployment. The lower level will include retirees and students. Income is measured by family income ratio to the federal poverty line (<100%, 100%-199%, 200%-399%, >400%). Health insurance will be categorised into private health insurance (including any private health insurance, Medi-Gap or single-service plan), public health insurance only (including Medicare, Medicaid, State Children’s Healthcare Plan, military healthcare, Indian Health Service, State Sponsored Health Plan or other government programme) and no health insurance. No data is available in NHANES on area deprivation.

Mental multimorbidity will include depression (“moderately-severe” or “severe” depressive symptoms versus “moderate”, “mild” or “no” depressive symptoms; as measured by the PHQ-9) and severe mental illness (as measured by medicines prescribed in the past month for severe mental illness).

Physical multimorbidity will be measured using Ronaldson et al. approach (**Supplementary Table 1**) (28). However, not all the 36 long term physical health conditions are reported in NHANES (such as bronchiectasis, psoriasis and polycystic ovarian syndrome). Only those that are available in NHANES will be used to indicate the physical multimorbidity construct.

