#### Mediators

Mediators are health behaviours and lifestyle, and C reactive protein.

Health behaviours and lifestyle variables will include obesity (BMI>=30), alcohol intake (healthy versus unhealthy level; the former is defined as daily consumption of one drink or fewer for women and two drinks or fewer for men, according to the dietary guidelines in the US - one drink contains 14g of ethanol in the US), smoking (healthy versus unhealthy levels; the former is defined as never smoked or smoking fewer than 100 cigarettes in life), physical activity (healthy versus unhealthy; the former is defined as 150 minutes of moderate-intensity physical activity weekly or 75 minutes of high-intensity physical activity weekly), poor appetite or overeating (Yes versus No), diet quality (healthy versus unhealthy; the former is defined as the health eating index in the top two fifths of distribution), trouble falling/staying asleep or sleeping too much (Yes versus No), ever addicted to any substance or behaviour (Yes versus No), number of sexual partners in the past year, inconsistent condom use (“never” versus “occasionally” or “always”), toothbrushing (twice daily versus less than twice daily), dental flossing (once daily versus less than once daily) and dentist visiting (once every two years or more versus less than once every two years).

The level of CRP is used as a marker of bodily inflammation and presented in mg/L.

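### CRP is assigned as a mediator but nothing places it before the conditions; in NHANES that order cannot be established, so an indirect effect through CRP to disease or admission cannot be read as a pathway

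*Protocol article*

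**What the plan says.** In the Protocol article, the Mediators section for UK BioBank states: "Mediators are health behaviours and lifestyle, and C reactive protein (as an indicator of systemic inflammation". The NHANES Mediators section gives CRP the same role: "Mediators are health behaviours and lifestyle, and C reactive protein". RELACHS has no inflammatory marker, so the point concerns two of the three datasets.

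The direction comes from the Introduction, where socioeconomic adversity and traumatic events "are linked to compounded mental and physical conditions via systemic inflammation and behavioural pathways". The Statistical analysis section then says: "In step three of the analysis, SEM will be used to examine the direct and indirect relationships between the constructs".

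The disease constructs are standing conditions. The UK BioBank physical construct "comprises a total of 36 long term physical health conditions", and participants were "aged between 40 and 69 years at the time of recruitment (2006 to 2010". NHANES uses those of the 36 conditions that it records, depressive symptoms, "severe mental illness (as measured by medicines prescribed in the past month for severe mental illness", and oral status by examination and self-report.

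The outcomes are mortality and hospitalisation. In UK BioBank both are counted from 01/01/2011. In NHANES, deaths are available to the end of 2015, while hospitalisation is taken from the twelve months before the survey.

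**The concern.** A mediator has to come after its cause and before its effect. If CRP is measured when the conditions are already present, a correlation between CRP and disease can arise because inflammation led to the disease or because the disease raised CRP. A model that contains only the first arrow assigns the whole correlation to it.

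The product of the adversity-to-CRP and CRP-to-disease paths would then be non-zero even if inflammation caused none of the disease. In samples of this size it could be highly significant and be read as evidence for an inflammatory mechanism. What is at stake is the interpretation of the CRP pathway. The test for synergistic interaction in step four is a separate analysis.

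**Working it through.** The plan gives no figure for this point, so there is none to reproduce. The check has two parts: the timing the article states, and an illustration of how large the ambiguity could be.

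**1. Timing, set side by side**

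- *NHANES, CRP and conditions.* The Design section describes questionnaires, examinations and laboratory tests within survey cycles. No later measurement of conditions is described. Long-term conditions, last-month prescriptions, attachment loss and tooth loss are states present at or before the survey.
- *NHANES, CRP and hospitalisation.* The admission falls in the year before the survey, and so before the survey's laboratory tests. A CRP-to-admission path runs backwards in time.
- *NHANES, CRP and death.* Death follows the survey. This is the only correctly ordered target for CRP.
- *UK BioBank.* The article dates neither the CRP sample nor the conditions. Recruitment was 2006 to 2010 and outcomes start in 2011, so if CRP is a recruitment measure, CRP to death or admission is correctly ordered. CRP to a condition is correctly ordered only if that condition arose after the sample.
- *Safeguards.* The article states no restriction to new conditions, no disease-to-CRP path and no comparison with the reverse order. The one time-related check, an intraclass correlation between baseline and follow-up exposure data, concerns stability rather than direction, and it is planned for UK BioBank and RELACHS, not NHANES.

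**2. Size under a fully reversed truth (all path values assumed)**

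Let A be adversity, D disease and C CRP, all standardised. Truth: A→D = a, D→C = d, and C→D = 0. Then r(A,D) = a, r(D,C) = d and r(A,C) = ad. Fit the mediation order A→C→D with a direct A→D path:

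- fitted A→C = ad
- fitted C→D = (d − a·ad)/(1 − (ad)²) = d(1 − a²)/(1 − a²d²)
- false indirect effect = product of the two
- share of the total effect a = d²(1 − a²)/(1 − a²d²); the true share is 0

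With a = 0.3:

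- d = 0.2: 0.060 × 0.183 = 0.011; share 0.0364/0.9964 = 3.7%
- d = 0.3: 0.090 × 0.275 = 0.025; share 0.0819/0.9919 = 8.3%
- d = 0.5: 0.150 × 0.465 = 0.070; share 0.2275/0.9775 = 23.3%

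With a and d each ranging from 0.1 to 0.4, the share runs from 0.8% (a = 0.4, d = 0.1) to 15.9% (a = 0.1, d = 0.4). Over both sets of assumptions it is roughly 1% to 23%.

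**3. Would it look significant, and would model fit reveal it?**

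One simulation with a = d = 0.2 at the UK BioBank size (n = 502,412) gave a false indirect effect of 0.0081 (exact 0.0077) and a Sobel z of about 29. Since z grows with √n, about 30,000 people (three NHANES cycles of nearly 10,000, before any exclusions) would give 29 × √(30,000/502,412) ≈ 7, ignoring the survey design.

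With three observed variables both orders are saturated and fit equally well. In that case CFI, TLI, RMSEA and SRMR cannot choose between them.

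**The case against.** The strongest reply is that the fitted paths are not visible. The Mediators sections list CRP without saying between what, and Figure 1 is not reproduced here. The Introduction sentence is background, and the same paragraph calls the links between conditions bidirectional. Step two makes mortality and hospitalisation the predicted outcomes. If CRP is meant to lie between the constructs and those outcomes, CRP raised by disease is part of the mechanism and no artefact. For UK BioBank this reply stands. For NHANES it helps only with death, because NHANES hospitalisation precedes the survey. Whichever way Figure 1 is drawn, a CRP path to conditions or to admission lacks a supportable order there.

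Several stronger readings are tempting, and the article does not support them:

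- A reader might infer that UK BioBank CRP was drawn after the conditions had developed. Age at recruitment and the long-term nature of the conditions make some overlap plausible, but neither date is given, and a condensed article may leave ascertainment windows to the full plan.
- A reader might infer that the CRP-to-disease path mostly measures disease raising CRP, or that a false pathway is certain to be reported. Both need a zero true effect and a strong reverse path, and neither is known. The three-variable shares also do not carry over directly to a model with latent constructs and many parallel mediators.
- A reader might point to psoriasis and bronchiectasis as inflammatory conditions. The article names these two as not reported in NHANES, where the timing problem is clearest, and it says nothing about their effect on CRP.
- A reader might conclude that the syndemic finding itself is undermined. The research questions do not ask about CRP mediation, and synergy is tested separately in step four.

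**Conclusion.** The concern holds in a limited form. For NHANES it follows from the stated design: CRP cannot be shown to precede the conditions, and it comes after the admissions, so an indirect effect through CRP to either cannot be separated from disease-driven CRP. No later analysis wording can supply that order. For UK BioBank the timing is unstated, so the ambiguity applies only to conditions already present at the blood sample. A path from CRP to later death or admission may be sound.

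The size of roughly 1% to 23% falsely mediated is an illustration. It assumes adversity-to-disease paths of 0.1 to 0.4, disease-to-CRP paths of 0.1 to 0.5, no true CRP effect and only three variables. It shows that the error need not be large to look convincing at these sample sizes; it does not estimate the bias in this study.

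**What to change.** **NHANES.** Estimate CRP mediation only towards later death. Report CRP's links with conditions and with prior-year hospitalisation as cross-sectional associations, and make no indirect-effect claim for them.

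**UK BioBank.** State when CRP was sampled and how conditions are dated. Treat conditions recorded before the sample as predictors of CRP, and base the mediation claim on the order (adversity and prevalent conditions) → CRP → later mortality or admission. The article describes linked records ("It benefits from data linkages to other health related records: primary care data, hospital admission data and cancer and death registries"), so an analysis of conditions first recorded after the sample is possible as an optional sensitivity analysis, for conditions that linkage can date. It should not be the main model. Excluding existing cases condition by condition gives a different at-risk sample for each of the 36 conditions, which does not fit a single latent multimorbidity construct, and linked dates are unlikely to cover the self-reported oral indicators.

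**Cost.** The NHANES change is wording and a shorter list of paths. It weakens the mechanistic claim from that dataset, and the remaining path to death has short follow-up: people surveyed in 2014 have at most about two years to the end of 2015. UK BioBank needs some extra work to date conditions against the sample.
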